### Data analysis

Due to the observational design of the study it is likely that there is an imbalance of prognostic factors between patients who are and patients who are not receiving PCT consultation. As a consequence the estimated effects of PCT consultation can be biased. We will adjust for imbalance in the statistical analysis by using propensity scores [40–42].

We will develop a propensity score model to assess the probability that a patient would have been offered PCT consultation. Patient characteristics to be included in this model are age, sex, marital status, primary diagnosis, reason for hospitalization (e.g. treatment of complex symptoms, palliative chemotherapy, treatment of complications), life expectancy, functional status, attending physician specialty, comorbidity, and hospital of admission [14, 16]. The logit of the propensity score will be used to match each patient receiving PCT consultation with one or more usual care patients.

Quality of life scores at different time points will be compared between the PCT and care as usual groups with repeated measurement analysis. A model will be fitted that includes matched-pairs, time, treatment group, the baseline score, and interaction between time and treatment group.

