**Methods/design:**

The study consists of 3 parts:

1. A questionnaire, interviews and a focus group discussion to investigate the characteristics of PCT consultation in 12 hospitals. PCTs will register their activities to calculate the costs of PCT consultation.

2. Cancer patients for whom the attending physician would not be surprised that they would die within 12 month will be included in a medical file search in three hospitals. Medical records will be investigated to compare care, treatment and hospital costs between patients with and patients without PCT consultation.

3. In the other nine hospitals, we will perform a longitudinal study, and compare quality of life between 100 patients for whom a PCT was consulted with 200 patients without PCT consultation. Propensity score matching will be used to adjust for differences between both patient groups. Patients will be followed for three months after inclusion. Quality of life will be assessed with the Palliative Outcome Scale, the EuroQol-5d and the EORTC-QLQ-C15 PAL. Satisfaction with care in the hospital is measured with the IN-PATSAT32. The cost impact of PCT consultation will also be explored.

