We aim to include 100 patients for whom a PCT was consulted and compare them with at least 200 patients receiving usual care. With such a sample size we will be able to detect a difference in quality of life as measured by the EORTC QLQ-C15 PAL at day 14 of 0.4 in standard deviation units (Cohen’s D = effect size) with alpha of 0.05 (2-sided) and power of 90 %.

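### Matching all of the minimum 200 controls 1:2 removes no imbalance, and the quality-of-life model otherwise adjusts only for the baseline score

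*Protocol article*

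**What the plan says.** The sample-size paragraph of the quality-of-life substudy states: "We aim to include 100 patients for whom a PCT was consulted and compare them with at least 200 patients receiving usual care". The abstract gives the comparison as 100 against 200. The target is a difference "at day 14 of 0.4 in standard deviation units", "with alpha of 0.05 (2-sided) and power of 90" per cent.

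The Data analysis section expects confounding: "it is likely that there is an imbalance of prognostic factors between patients who are and patients who are not receiving PCT consultation". Its answer is a propensity model with ten characteristics, the last three being "attending physician specialty, comorbidity, and hospital of admission". On use of the score it says: "The logit of the propensity score will be used to match each patient receiving PCT consultation with one or more usual care patients". On the outcome analysis it says: "A model will be fitted that includes matched-pairs, time, treatment group, the baseline score, and interaction between time and treatment group".

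Two features matter here. The number of controls per consulted patient is open in the matching sentence, whereas the model sentence speaks of pairs. And the listed model terms include the baseline score but none of the ten propensity characteristics.

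**The concern.** Matching improves balance by leaving out controls who do not resemble the treated patients. When the control pool is only twice the treated group, a 1:2 match leaves nobody out. The matched sample is then the full sample, and the only case-mix adjustment left is the baseline score.

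The power statement is built on 100 against 200, so an analyst who wants to keep the stated power at the minimum pool is drawn towards exactly that match. If consulted patients are sicker, as one might suspect, the remaining bias works against consultation. The same quality-of-life measure is also the effect measure in the cost-effectiveness ratio (Economic evaluation), so the bias would carry over.

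**Working it through.** **1. The plan's own figure.** Inputs from the sample-size paragraph: d = 0.4, two-sided alpha 0.05, 100 v 200. Normal approximation: power = Φ(d / √(1/n₁ + 1/n₂) − 1.96).

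- 100 v 200: 0.4/√0.015 = 3.27, and Φ(1.31) = 90.4% (noncentral t: 90.2%). The stated 90% reproduces and uses all 200 controls.
- 100 v 100: 0.4/√0.02 = 2.83, and Φ(0.87) = 80.7% (noncentral t: 80.4%).

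**2. What a 1:2 match from 200 does.** In set *i*, let T be the consulted patient's value and C₁, C₂ the two controls' values. The mean within-set difference over 100 sets is

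(1/100) Σ [Tᵢ − (C₁ᵢ + C₂ᵢ)/2] = mean(T) − (sum of all 200 controls)/200 = mean(T) − mean(C).

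This is the crude difference, however the sets are formed. It is exact for complete data and holds for any outcome or covariate, so set terms in the model do not change the group contrast.

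**3. Imbalance left under other matching rules.** Simulated optimal matching of all 100 consulted patients on a normal logit score with equal SDs; with replacement, nearest neighbour. The article gives no raw gap, so it is varied as an assumption. Entries are the gap remaining, in SD.

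| Raw gap | 1:2 from 200 | 1:1 from 200 | 1:2 from 300 | 1:1 from 200, with replacement |
|---|---|---|---|---|
| 0.3 | unchanged | 0.02 | 0.04 | under 0.01 |
| 0.5 | unchanged | 0.05 | 0.11 | 0.01 |
| 0.75 | unchanged | 0.16 | 0.28 | 0.01 |
| 1.0 | unchanged | 0.32 | 0.52 | 0.02 |

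A variable ratio of 1 to 5 controls leaves 0.05 of a 0.5 gap and 0.15 of a 0.75 gap, about the same as 1:1.

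**4. Bias in quality of life with the planned model.** Simulation with no true effect, 100 v 200, and two prognostic covariates each differing by the stated gap. The model has set effects and the baseline score. Ranges span repeated sets of simulated studies (200 or 400 per scenario). Bias is in outcome SD and runs against consultation when consulted patients are sicker.

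| Covariate gap | 0.3 | 0.5 | 0.7 |
|---|---|---|---|
| Crude, and 1:2 sets without baseline | 0.20 | 0.34 | 0.47 |
| 1:2 with baseline | 0.10–0.12 | 0.17–0.19 | 0.24–0.26 |
| False rejection at 5%, 1:2 with baseline | 17–22% | 40–50% | 65–73% |
| 1:1 with baseline, no caliper | 0–0.02 | 0.03–0.06 | 0.09–0.10 |
| False rejection at 5%, 1:1 with baseline | about 5% | about 8% | 14–16% |

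Adding the two covariates to the model brings bias to within about 0.01 SD and rejection to about 4–8%, at both ratios.

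The crude row shows how strong the assumed confounding is: 0.20/0.3, 0.34/0.5 and 0.47/0.7 are all about 0.67. So the outcome moves about 0.67 SD when both covariates move 1 SD.

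**5. A simpler check with other assumptions.** Let case mix correlate *a* with both baseline and outcome, let baseline and outcome correlate *r*, and let the gap be *d*. With no selection, bias is *a·d* before and *a·d*(1 − *r*) after baseline adjustment. With *a* = 0.3, *r* = 0.5, *d* = 0.75: 0.3 × 0.75 = 0.225, then 0.225 × 0.5 = 0.11. With *r* = 0.5 throughout, the adjusted bias runs from 0.05 (*a* = 0.2, *d* = 0.5) to 0.25 (*a* = 0.5, *d* = 1.0).

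**The case against.** The strongest reply is that the harmful case is not what the article prescribes. It needs three things together: a fixed 1:2 ratio, no replacement and exactly 200 controls. The text allows one or more controls per patient, is silent on replacement and treats 200 as a floor. A reader might infer that the plan, as written, adjusts for nothing; the document does not support that. Nor does it support reading a ban on calipers into the word each. Caliper, replacement and ratio rules commonly sit in an analysis plan that is not shown, so their absence is no error. All of this stands.

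It is also tempting to say that matching is the only protection. It is not: the baseline score is in the model, and in the simulation it removes nearly half of the crude bias (0.34 to 0.17–0.19 at a gap of 0.5).

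Nor is 1:1 a serious problem by itself. Its bias is small up to a gap of about 0.5 SD. The power loss can be overstated too: if baseline and outcome correlate 0.5, the effective standardised effect is 0.4/√(1 − 0.25) = 0.46, and 100 v 100 has about 90% power; at a correlation of 0.3 it is about 84%. So one cannot say that the study must lose either its power or its adjustment.

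Finally, the covariate gaps are assumptions, and the fix does well partly by construction, because the model is given the very covariates that created the confounding. That limits what the simulation promises, but it does not favour leaving known, collected prognostic factors out of the model.

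What survives is the algebra of step 2, the fact that the stated power corresponds to that configuration, and a listed outcome model with nothing but the baseline score to fall back on.

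**Conclusion.** The point holds conditionally. If the minimum of 200 controls is used in full, 1:2 and without replacement, matching removes none of the imbalance; this is arithmetic and needs no assumption about case mix. The size of the consequence does rest on assumptions. With covariate gaps of 0.3 to 0.7 SD and the confounding strength shown above, the bias left after baseline adjustment is roughly 0.10 to 0.26 SD, that is 25% to 65% of the 0.4 SD design effect (0.10/0.4 and 0.26/0.4). Weaker confounding gives less, down to 0.05 SD in the cases checked.

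At 1:1 the bias is about 0.04 SD at a gap of 0.5 and about 0.1 SD at 0.7, with power near 80% before any gain from the baseline score. More controls reduce the problem, and replacement nearly removes the imbalance on the score. This should be fixed because the remedy protects the estimate whichever ratio is chosen. It is not a fatal flaw, since the article does not commit to the harmful match.

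**What to change.** Keep the propensity matching and make three changes to the Data analysis section.

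- Add to the repeated-measures model the main prognostic covariates already collected for the propensity score: age, primary diagnosis, comorbidity, functional status, life expectancy and reason for hospitalization.
- Replace matched pairs by matched sets, so that the model agrees with a matching rule that permits more than one control.
- State that a fixed 1:2 match that uses up the whole control pool will not be relied on as the adjustment for case mix.

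The cost is a few lines of text and a few degrees of freedom, more for the multi-category factors; lower residual variance usually repays it. No new data are needed. The change deals with measured covariates only; unmeasured differences between the groups remain a limit of the observational design.

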### Palliative care team consultation in hospitals in the Netherlands

The Netherlands has a nationwide system of palliative care consultation services, that is predominantly used by general practitioners for patients staying at home [30–32]. More recently, hospitals have started establishing PCT consultation services. An inventory of the Comprehensive Cancer Centre Netherlands in 2013 showed that at least 45 hospitals in the Netherlands, out of a total of 92, were in different stages of implementing such consultation services [33]. Most hospital-based specialist PCTs can be consulted by physicians or nurses working in the hospital. Upon their involvement, PCTs typically provide a detailed holistic assessment of the patients’ and family´s situation. They assess patients’ symptoms and their physical, emotional, social and spiritual problems, prioritize these and propose a care plan to address them. The extent to which PCTs provide care themselves or only advise the primary caregivers varies. Most PCTs consist of professionals from different specialties, such as oncologists, neurologists, anaesthesiologists, nurses, and psychosocial and spiritual caregivers. The structure and activities of PCTs in hospitals vary. Some PCTs are strongly embedded in the hospital and supported by their hospital boards, whereas others are not. Some teams are involved in education within or outside the hospital.

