### The effect of PCT consultation for patients with incurable cancer on quality of life and the cost effectiveness of PCT consultation

In 9 hospitals we will study the effect of PCT consultation for in-hospital patients with incurable cancer on quality of life. In order to get a good overview of different types of hospitals, a university hospital, teaching and general hospitals will be included. In order to include sufficient comparable patients receiving usual care 3 hospitals without a PCT will be included.

Inclusion criteria are that patients are 18 years or over; that the attending physician answers “no” to the question “Would you be surprised if this patient would die in the next year?”; and that the patient is expected to stay in the hospital for at least 3 days. The latter criterium is added to enable an informed consent procedure. Patients will be included upon arrival in the hospital. Eligible patients will receive an information letter, and will be informed and asked to participate by an attending nurse. Patients who agree to participate will be followed during three months, regardless of where they stay. The attending physician will be asked to fill in a questionnaire to assess medical information such as diagnosis, performance status, co morbidity and life expectancy. Palliative care consultation teams are asked to fill a questionnaire about the content of the consultation. Patients will be asked to fill out a number of subsequent questionnaires. In these questionnaires, quality of life is assessed with the EORTC QLQ-C15 PAL [34]. We will also measure quality of life with the Palliative Outcome Scale [35] and the EuroQol-5D [36] , because of the lack of consensus on the most appropriate quality of life instrument for patients with incurable disease [37]. Secondary measures are symptom scores for pain, dyspnoea and anxiety (EORTC QLQ-C15); patient satisfaction with care, using the INPATSAT 32 questionnaire [38, 39]. Quality of life will be assessed longitudinally at six moments in time: at day 4, 7, 14, 30, 60 and 90 after admission to the hospital; satisfaction with care will be assessed at day 14 after admission.

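### The quality-of-life model has no hospital term: if controls from the three hospitals without a PCT are kept, as intended, its standard error is too small; if hospital stays in the propensity score, they supply no controls

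*Protocol article*

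**What the plan says.** The protocol article, Methods, describes substudy 3 thus: "In 9 hospitals we will study the effect of PCT consultation for in-hospital patients with incurable cancer on quality of life". The hospitals are meant to differ: "In order to get a good overview of different types of hospitals, a university hospital, teaching and general hospitals will be included". Three of them are there for one purpose: "In order to include sufficient comparable patients receiving usual care 3 hospitals without a PCT will be included". The Background remarks of Dutch hospitals in general that "The structure and activities of PCTs in hospitals vary".

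The sample size is set out as "We aim to include 100 patients for whom a PCT was consulted and compare them with at least 200 patients receiving usual care". The detectable difference on the EORTC QLQ-C15 PAL is one "at day 14 of 0.4 in standard deviation units", "with alpha of 0.05 (2-sided) and power of 90" percent. No ICC or design effect is mentioned.

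Data analysis lists the admitting hospital among the covariates of the propensity score. It matches each PCT patient to one or more usual-care patients on the logit of that score, and does not require matches to come from the same hospital. The outcome model is then given: "A model will be fitted that includes matched-pairs, time, treatment group, the baseline score, and interaction between time and treatment group".

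**The concern.** Patients in one hospital share staff, case mix and habits of care, so their outcomes may be correlated. A model without a hospital term gives that correlation no place. This matters when the share of PCT patients differs between hospitals in the analysed set, and it matters most when some hospitals contribute controls only. The PCT contrast is then partly a comparison of hospitals, and nine hospitals carry much less information on that than 300 patients appear to.

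The matched-set term does not stand in for hospital, because sets formed on the propensity logit need not lie within one hospital. What is at stake is the 5% error rate and the 90% power of the main quality-of-life comparison, whose estimate also feeds the cost-effectiveness ratio.

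**Working it through.** **Inputs from the article.** 100 PCT and 200 usual-care patients; difference 0.4 SD; two-sided alpha 0.05; nine hospitals in substudy 3, three without a PCT. Strengths and weaknesses counts 12 hospitals and 9 PCTs. Taking the three substudy 2 hospitals to have PCTs, six PCT hospitals remain in substudy 3 (an inference).

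**Assumptions.** The article gives no hospital ICC, so 0.02, 0.05 and 0.10 are used. Total variance is set to 1.

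**1. The plan's own figure.** With independent patients the variance of the difference is 1/100 + 1/200 = 0.015. Power = Φ(0.4/√0.015 − 1.96) = Φ(1.306) = 90.4% (90.2% with the t distribution). The stated 90% is reproduced, but only with no hospital variance.

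**2. Controls from the three hospitals are kept.** Equal recruitment gives 300/9 = 33.3 patients per hospital. The six PCT hospitals then hold 200 patients, 100 PCT and 100 usual care, and the other three hold 100 usual-care patients. With a random hospital effect,

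Var = ICC × S + (1 − ICC) × 0.015,

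where S is the sum over hospitals of (share of PCT patients − share of usual-care patients)². Here S = 6 × (1/6 − 1/12)² + 3 × (1/6)² = 0.0417 + 0.0833 = 0.125.

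Actual type I error = 2 × [1 − Φ(1.96 × √(0.015/Var))]. Power of the crude comparison with the correct standard error = Φ(0.4/√Var − 1.96).

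| ICC | Var | Var / 0.015 | Type I error | Power |
|---|---|---|---|---|
| 0.02 | 0.0172 | 1.15 | 6.7% | 86% |
| 0.05 | 0.0205 | 1.37 | 9.4% | 80% |
| 0.10 | 0.0260 | 1.73 | 13.7% | 70% |

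**3. Hospital stays in the score.** In a hospital with no PCT the fitted propensity is close to 0, so its patients have no PCT counterpart on the logit scale. If all controls come from the six PCT hospitals in proportion, S = 0 and Var = (1 − ICC) × 0.015. The ratio of the true standard error to the one that ignores hospital is √(1 − ICC) = 0.990 / 0.975 / 0.949, and the type I error is 4.8 / 4.4 / 3.9%. The model's standard error is then slightly too large. The cost lies in numbers: with the 100 controls of step 2, Var = 1/100 + 1/100 = 0.02 and power = Φ(0.4/√0.02 − 1.96) = Φ(0.868) = 80.7%. Power of 90% needs 99 PCT and 198 usual-care patients.

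**4. Simulation of the matching.** Assumed: nine hospitals of 34 patients, uneven PCT use over six, one covariate, 1:1 caliper matching on the logit, a paired t test without hospital, 1,500 runs per cell. The Monte Carlo standard error at 5% is √(0.05 × 0.95/1500) = 0.6 points.

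| | Hospital in score | Hospital left out |
|---|---|---|
| Controls from non-PCT hospitals | 0% | about 52% |
| Pairs within one hospital | 30% | 7% |
| Pairs formed | about 68 | about 99 |
| Type I error, ICC 0.02 / 0.05 / 0.10 | 5.5 / 4.2 / 4.5% | 5.8 / 8.5 / 16.1% |

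A second simulation gave 5.2 / 4.3 / 4.0% with hospital in the score and 6.0 / 10.7 / 16.5% without it. In the latter case, hospital fixed effects in the outcome model brought the error to 5.7 / 4.5 / 6.7%.

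**The case against.** A reader might infer from the missing term that the standard errors are too small and the false-positive rate above 5% as the plan stands. The documents do not support that. Hospital is in the propensity score, and a literal reading excludes the non-PCT hospitals from matching; steps 3 and 4 then show no inflation. This objection stands, and it makes the point conditional. It does not remove the point, because the article says that the three hospitals were added to provide controls, and the score as specified prevents that.

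The calculation in step 2 is an unmatched comparison of means. Baseline adjustment may absorb part of any stable hospital difference, so the relevant ICC is a residual one and may be lower. That stands. The figures illustrate a range.

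The 70% power is not what a hospital-adjusted analysis would have. In the step 2 layout, the contrast within the six PCT hospitals alone has variance (1 − ICC) × 0.02, which is 0.019 / 0.018 at ICC 0.05 / 0.10 and gives about 83% / 85% power. That also stands, and it favours adding the term.

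The article is condensed, and its list of terms need not be complete. Random-effect structure and degrees of freedom can reasonably sit in an analysis plan. The conflict between the recruitment of the three hospitals and the matching model, however, is in the article itself.

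Finally, the Background remark on varying PCTs concerns Dutch hospitals in general and is weak evidence about these nine.

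**Conclusion.** The point holds in conditional form. As written, the plan can go two ways, and neither gives both 5% and 90% unless the PCT hospitals alone supply about 200 matchable controls. The stated reason for adding three hospitals without a PCT suggests that this was not expected.

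- If their patients are retained, the test without a hospital term is too liberal, with the errors and crude power of step 2. This rests on an assumed ICC of 0.02 to 0.10, half the controls from those hospitals, and equal recruitment.
- If hospital stays in the score, the error rate is sound or slightly conservative, but the three hospitals contribute nothing to the matched comparison and power may fall to about 81%.

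It is also tempting to carry the point over to the cost and hospital-day comparisons of substudy 2. The article lists no model terms for these, and three hospitals are too few to estimate a hospital variance, so that extension is not supported.

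**What to change.** First, reconcile the recruitment text with Data analysis: state whether and how patients of the three non-PCT hospitals enter the matching, and whether hospital stays in the score. If they are not to be matched, restate the expected number of controls and the power.

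Second, add a hospital effect to the repeated-measures quality-of-life model of substudy 3: a random intercept with small-sample degrees of freedom (for example Kenward-Roger), since there are only nine hospitals. Fixed hospital effects also protect the error rate, but then the three non-PCT hospitals carry no information on the within-hospital PCT effect. A random intercept does not remove confounding between hospitals, so the statement on matching is needed in either case. Do not extend the random intercept to substudy 2.

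The cost is one model term and a sentence or two on matching. If non-PCT controls are retained, intervals may be noticeably wider. With known variances, the random-intercept estimate is at least as precise as the better of the crude and within-hospital contrasts. In the step 2 layout its standard error is therefore at most √(0.0172/0.015) = 1.07, √(0.019/0.015) = 1.13 and √(0.018/0.015) = 1.10 times the one that ignores hospital, at ICC 0.02, 0.05 and 0.10. The small-sample correction adds to this. If those controls are not used, the term costs almost nothing.
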